**Design::**

A multiphase study with a descriptive cross-sectional questionnaire phase 1 and a phase 2 cluster randomized controlled trial (RCT), conceptualized to determine the effectiveness of a school-based ‘tobacco free’ health education intervention on adolescents’ knowledge and attitude towards SHS.

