With a design effect at 1.5 and a non-response at 5%, the final sample size was calculated to be 1400 for the Phase 1 study.

*For phase 2: (Randomized controlled trial)*

The sample size calculation for Phase 2 randomized controlled trial was done using G Power 3.1.2. We calculated a total sample size of 250 with125 in the control group and 125 in the intervention group, 90% power, an Effect size of 0.3, confidence interval at 95% and attrition at 10%.

*Recruitment and eligibility*

The study is now recruiting and the criteria for eligibility are as follows, 

*Inclusion criteria for phase 1 study *

1. All Schools in Mangalore who have primary and secondary schools in the same campus.

2. Those schools who consent to participate in the study

3. Students whose parents give written informed consent and they themselves give informed assent.

*Exclusion criteria for phase 1 study*

1. Participants who are self-reported smokers.

*Inclusion criteria for phase 2 study *

1. Inclusion criteria: Participants with salivary cotinine levels of > 0.1 ng/mL

2. Exclusion criteria: Participants whose sibling is already a participant in the study

*Study procedure*

*Phase 1*

The first phase will be a descriptive cross-sectional study. A cluster random sampling of all the schools in Mangalore will be done to obtain the required sample size of 1,400. A questionnaire will then be administered to the 12 year olds in the selected schools, who fulfil the inclusion criteria. 

*Questionnaire*

Demographic data will be recorded. Socioeconomic status will be assessed using the BG Prasad Scale (Prasad., 1961) modified considering the base of Consumer Price Index (CPI) for 2017 (Singh et al., 2017). The questionnaire will have two components, one to assess children’s exposure to SHS using Questionnaire 1 which has 5 questions (Lin et al., 2010). The second component, Questionnaire 2, is a 25 item questionnaire (Gharaibeh et al., 2011) to determine Children’s knowledge, attitude and behaviour towards second hand smoke. Knowledge will be assessed using 10 items, Attitude with 5 items, Avoidance behaviour towards second hand smoke will be assessed using 5 items and Self-efficacy of avoidance will be assessed using 5 items. This assessment will be carried out at the start of Phase 1 and at all 3 follow-up time points in Phase 2.

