The questionnaire will be administered to 10 individuals and reliability measured using the Cronbach’s coefficient alpha. A high coefficient indicates that the items are consistently measuring the same underlying construct.

Data will be analysed and those students who report exposure to second hand tobacco smoke will be selected and their salivary cotinine level checked.

*Salivary Cotinine level estimation*

Children’s exposure to SHS will be determined by measuring their salivary cotinine levels twice, one at the end of Phase 1(baseline) and second at the 3rd follow-up, i.e., at 12 months after the intervention. Salivary cotinine is a sensitive biochemical marker which is strongly associated with exposure to SHS. It has a half-life of 16 hours and is a widely recognized marker for detecting both active and passive smoking. 

Saliva collection: Saliva will be collected not before at least 60 minutes after a major meal. Participant will be asked to rinse mouth thoroughly with water 10 minutes before sample is collected. The head is tilted forward, allowing the saliva to pool on the floor of the mouth. Whole saliva will be collected in a labelled vial by unstimulated passive drool. After collection, sample will be refrigerated within 30 minutes, and frozen at or below -20ºC within 4 hours of collection. 

Salimetrics^®^ High Sensitivity Salivary Cotinine Quantitative Enzyme Immunoassay Kit will be used for cotinine estimation in saliva (Salimetrics., 2018). There will not be any personal identifiers on the vials sent to the laboratory and individual results will not be disclosed.

The participants who have salivary cotinine levels of > 0.1 ng/mL will be selected and they will form the sampling frame for the second phase of the study which will be a randomized controlled trial.

*Phase 2*

This phase will be a randomized controlled trial, with a sample size of 250, 125 participants in the intervention group and 125 in the control group.

Random allocation: Sequence generation will be done using the table of random numbers. We will adopt the process of first identifying potential individual participants in each cluster, recruiting these participants and then do cluster randomisation. Allocation concealment will be done using sequentially numbered, opaque, sealed envelopes (SNOSE). The study will be outcome assessor blinded.

*Intervention*

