The intervention consists of 40 min ‘tobacco free’ health education session delivered once a week for 3 consecutive weeks by the principal investigator (PI) (AR). The first session will address tobacco and its adverse effects. The second session will be on laws regarding tobacco in India and the World and the third session will be on how to prevent exposure to tobacco. Teaching methods include lectures, demonstrations, discussions, storytelling and quiz. Children are also given take home brochures every week that contains messages on the effects of tobacco and how to make their homes smoke-free.

There will be 3 follow up time points. The first follow up will be at the 3rd month, second follow up at the 6th month and the third follow up at 12 months after the intervention. On the first day of each follow up, the PI will reinforce the key points of the intervention and also discuss with the students regarding their experiences at home and the challenges they faced. The timeline is given in Appendix 2. Participants in the control arm will receive conventional standard health education once, whereas those who report tobacco use will be encouraged to participate in tobacco counselling.

*Study outcomes*

To assess if there is any change in the salivary cotinine levels and the knowledge, attitude and behaviour scores of the participants after a ‘tobacco free’ health educational intervention.

To develop effective school-based intervention to reduce exposure and improve adolescents’ knowledge and attitude towards Second Hand tobacco Smoke and to promote smoke free homes.

*Data analysis plan*

Analysis will be done based on both the Intention to Treat and Per Protocol analysis. The data will be entered into the SPSS software (IBM Corp. Released 2011. IBM SPSS Statistics for Windows, Version 20.0. Armonk, NY: IBM Corp.) and analysed. Descriptive statistics will be presented and sub group analysis will be done wherever needed. The level of significance will be kept at 0.05 with 95% confidence levels. For the phase 1 study, Chi square test will be done for categorical variables and Independent sample t test will be done to compare means. Logistic regression will be done to obtain the adjusted odds ratio. For the phase 2 study, Paired sample t - test will be done.

*Ethical aspects*

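### Phase 2 is randomised by cluster, but its stated sample size makes no visible allowance for clustering, and its only named test has no cluster term and does not compare the arms

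*Protocol article*

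**What the plan says.** The Design paragraph of the abstract calls Phase 2 a cluster randomised trial. The random allocation paragraph of Materials and Methods gives the procedure: children are identified within each cluster, with "recruiting these participants and then do cluster randomisation".

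The sample size section treats the two phases differently. For the Phase 1 survey the calculation continues "With a design effect at 1.5 and a non-response at 5" per cent, to reach 1400. For Phase 2 it says "We calculated a total sample size of 250 with125 in the control group and 125 in the intervention group", with "90% power, an Effect size of 0.3, confidence interval at 95% and attrition at 10" per cent, computed in G Power. Neither the test family nor the kind of effect size is named.

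The data analysis plan gives one sentence to the trial phase: "For the phase 2 study, Paired sample t - test will be done". The same section promises intention-to-treat and per-protocol analyses but names no other Phase 2 method.

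**The concern.** In a cluster randomised trial a whole cluster receives one allocation, so the arm effect is estimated from differences between clusters. Here the intervention is also taught in sessions with discussion and quizzes, which can make children in one cluster resemble each other further. An arm comparison that treats children as independent then has standard errors that are too small, and a sample size without an inflation factor overstates power.

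The named test raises a prior problem. A paired t-test asks whether an arm changed from its own baseline. It does not use the control arm, so any change over 12 months that would have happened anyway can pass for an effect. The abstract hopes to see the programme in the school curriculum, and that claim needs a valid contrast between arms.

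**Working it through.** **Inputs from the article.** N = 250 (125 per arm), effect size 0.3, 90% power, significance level 0.05 (taken as two-sided), attrition 10%, so 112.5 completers per arm. Phase 1: P = 0.29, margin 0.03, design effect 1.5, non-response 5%, n = 1400.

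**Assumed, because the article does not give them.** ICC, number of clusters K, children per cluster m, and that 0.3 is a standardised difference d between arms.

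**Step 1: reproduce the stated sizes.**
- Phase 1: 1.96² × 0.29 × 0.71 / 0.03² = 879; 879 × 1.5 / 0.95 = 1388, consistent with 1400. The design effect is visible and used.
- Phase 2, two-sample t-test, d = 0.3, 90% power: 235 per arm, 470 in total, before attrition or clustering. This does not give 250.
- Phase 2, paired t-test within one arm, standardised change 0.3: 119 children, and 119 / 0.9 gives 133 after attrition. This is near 125 but not equal to it. Power of the paired test is 91% at 125 and 88% at 112.5.

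So 250 is closest to a before-after calculation within each arm, with no visible room for a design effect.

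**Step 2: power for an arm comparison with no clustering.** Two-sample t-test, d = 0.3: 66% with 125 per arm and 61% with 112.5 per arm.

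**Step 3: add clustering.** Design effect DE = 1 + (m − 1) × ICC. Effective n per arm = 112.5 / DE. True type I error of a naive two-sample test = 2 × [1 − Φ(1.96 / √DE)]. Power is that of the two-sample t-test at the effective n.

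The case anchored in the article takes the ICC implied by Phase 1. If 1400 children are spread evenly over K schools, ICC = 0.5 / (1400/K − 1). If the same K schools are the Phase 2 clusters, m = 250/K.
- K = 10: ICC = 0.5/139 = 0.0036; DE = 1 + 24 × 0.0036 = 1.086.
- K = 40: ICC = 0.5/34 = 0.0147; DE = 1 + 5.25 × 0.0147 = 1.077.

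| Case | DE | Effective n per arm | Type I error, naive two-sample test | Power, d = 0.3 |
|---|---|---|---|---|
| No clustering | 1.00 | 112.5 | 5.0% | 61% |
| ICC implied by Phase 1, K = 10 to 40 | about 1.08 | 104 | about 6% | about 58% |
| m = 10, ICC 0.05 | 1.45 | 77.6 | 10.4% | 46% |
| m = 25, ICC 0.05 | 2.20 | 51.1 | 18.6% | 32% |

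The table leaves out the further loss from having few between-cluster degrees of freedom.

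**Step 4: split the shortfall from 90%.** From 90% to 61% is 29 points, none of it due to clustering. Clustering then takes about 3 points in the Phase 1 case, 15 points at m = 10 with ICC 0.05, and 29 points at m = 25 with ICC 0.05.

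**The case against.** Four points can be made for the plan.

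- **It is a condensed article.** The number of clusters and the ICC may stand in the full protocol, and the Phase 2 flow figure is not shown. This stands: their absence alone is no finding. But the article does list its Phase 2 inputs and does name its Phase 2 test. A fuller document with a cluster-adjusted between-arm model would contradict that text.
- **The clustering may be mild.** This stands too. The only ICC that can be drawn from the article gives a design effect of about 1.08. The larger figures rest on an assumed ICC of 0.05. Nor should 1.5 be moved to Phase 2 unchanged: it belongs to 35 to 140 children per school, against about 6 to 25 in Phase 2 on the same spread.
- **The inflated error rates are not those of the planned test.** Correct. A reader might infer that the paired test has a false-positive rate of 10% to 19%. The documents do not support that. Stable differences between schools cancel in paired changes, and the relevant ICC is that of the changes, which is unknown. Shared teaching could make it positive.
- **Baseline adjustment could rescue 250.** With a baseline to follow-up correlation of 0.72, the two-sample normal-approximation size of 233.5 per arm becomes 233.5 × (1 − 0.72²) = 112.5, or 125 after 10% attrition. The article states no such correlation and names no adjusted analysis, and this too leaves nothing for clustering.

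A reader might also blame clustering for the whole fall from 90%. Step 4 shows otherwise: with a small ICC most of the gap is there before clustering enters.

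**Conclusion.** The point holds in this form: the stated analysis and the stated 90% power do not fit the stated cluster design. The named test neither compares the arms nor accounts for clusters, and the listed inputs show no clustering allowance although Phase 1 has one. For an unadjusted arm comparison at d = 0.3, power is about 61% with the planned completers before clustering. It is about 58% under the Phase 1 ICC and 32% to 46% under the two ICC 0.05 cases. The type I error of a naive arm comparison would be about 6% in the first of these settings and 10.4% to 18.6% in the others.

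The direction is certain for any positive ICC. The size rests on assumed ICCs and cluster sizes, on reading 0.3 as a between-arm standardised difference, and on no baseline adjustment.

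**What to change.** 1. **Analysis.** Replace the paired t-test as the Phase 2 effectiveness analysis with a between-arm comparison that respects the unit randomised. Either fit a mixed model of the follow-up value, adjusted for baseline, with a random intercept for cluster and small-sample degrees of freedom (Satterthwaite or Kenward-Roger), or use a t-test on cluster mean changes with K − 2 degrees of freedom. Paired changes within an arm can remain as description.
2. **Sample size.** Name the cluster unit, the number of clusters and the children per cluster. Restate the power of 250 for the comparison in item 1, using 1 + (m − 1) × ICC over a stated ICC range, and give any baseline correlation relied on. An ICC from Phase 1 is a rough guide only: it describes baseline answers from all surveyed children, whereas Phase 2 follows a subset selected on cotinine, with outcomes to 12 months after group teaching.

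The analysis change costs new wording and a different procedure. Confidence intervals will be wider, and the stated power will probably fall below 90%. Rewording does not restore that power. The study is already recruiting, so the sponsor would have to accept the lower figure or consider more clusters.

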**Methods::**

Baseline assessment will include a questionnaire followed by estimation of salivary cotinine levels. The experimental arm will receive the ‘tobacco free’ intervention, which includes 40 min health education session delivered once a week for 3 consecutive weeks. Participants will also be given ‘take home brochures’ every week containing messages on the effects of tobacco and how to make their homes smoke-free. The sample of 250 participants, for the Phase 2 RCT, with salivary cotinine levels of > 0.1 ng/mL will be selected from the participants of the Phase 1 study. The effect of the intervention will be quantitatively assessed by estimating the salivary cotinine levels after the intervention. Participants in the control arm will receive conventional standard health education once.

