## Materials and Methods

*Study setting*

The study will be conducted among 12 year old school children of Mangalore, India. 

*Broad objective:*

To contribute toward national efforts to protect children from harmful effects of SHS, the objective of this study is to develop effective school-based intervention to reduce exposure and improve adolescents’ knowledge and attitude towards Second Hand tobacco Smoke and to promote smoke free homes.

*Specific objectives*

To assess exposure to second hand tobacco smoke among 12 year old school children.

To carry out a school based ‘*tobacco free*’ educational intervention program among 12 year old school children.

To assess the Salivary Cotinine level as well as the knowledge, attitude and avoidance behaviour towards second hand tobacco smoke among 12 year old school children, before and after carrying out an intervention. 

*Study design and registration*

This will be a multiphase study using multiphase sampling technique among adolescents in Mangalore, India. The first phase will be a descriptive cross-sectional study. A cluster random sampling of all the schools in Mangalore will be done to obtain the required sample size of 1400. A questionnaire will then be administered to the 12 year olds in the selected schools, who fulfil the inclusion criteria. Data will be analysed and those students who report exposure to second hand tobacco smoke will be selected and their salivary cotinine level checked until we get a sample of 250 subjects with salivary cotinine levels of > 0.1 ng/mL (Avila-Tang et al., 2012). These will form the sample for the second phase of the study which will be a randomized controlled trial. (Figures 1 and 2). 

The protocol follows SPIRIT guidelines (Chan et al., 2013) and includes all items from the World Health Organization Trial Registration Data Set (WHO., 2019) [Appendix 1]. The trial has been registered with the Clinical Trial Registry of India (CTRI) with number CTRI/2018/09/015706 (Registered on 13/09/2018).

*Sample size calculation*

*For phase 1: (Cross-sectional study)*

The sample size estimation was done using the formula:

$n=\frac{{\left(Z_{1-a/2}\right)}^{2}\mathrm{PQ}}{d^{2}}$

where: 

Z_1-α/2_ = 1.96 (when α is 5% at 95% confidence limits)

P= Proportion of the event in the population (29%) (Singh et al., 2011)

Q=1-P (0.71)

d= Acceptable margin of error (3%)

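### No single outcome decides whether the intervention worked: the abstract shifts between knowledge and attitude and cotinine, and the outcomes section leaves four outcomes unranked

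*Protocol article*

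**What the plan says.** All references are to the Protocol article.

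- **Abstract, Design:** the trial is to determine the effectiveness of a "health education intervention on adolescents’ knowledge and attitude towards SHS". Cotinine is not mentioned.
- **Abstract, Methods:** "The effect of the intervention will be quantitatively assessed by estimating the salivary cotinine levels after the intervention". The scores are not mentioned.
- **Materials and Methods, Broad objective:** the aim is to "develop effective school-based intervention to reduce exposure and improve" knowledge and attitude, so exposure and scores stand together.
- **Study outcomes:** "To assess if there is any change in the salivary cotinine levels and the knowledge, attitude and behaviour scores of the participants". No outcome is called primary. The second item in this section, developing an intervention, is an aim rather than an outcome.
- **Questionnaire:** there is a fourth scale, "Self-efficacy of avoidance will be assessed using 5 items", which Study outcomes does not list. On timing: "This assessment will be carried out at the start of Phase 1 and at all 3 follow-up time points in Phase 2".
- **Salivary Cotinine level estimation:** cotinine is measured at baseline and once more, at 12 months.
- **Data analysis plan:** "The level of significance will be kept at 0.05". Both intention-to-treat and per-protocol analyses are planned, subgroups are left open, and the Phase 2 test is named without an outcome or visit.
- **Sample size calculation, Phase 2:** 250 children, 125 per arm, 90% power, effect size 0.3, 10% attrition. The 0.3 is not attached to any outcome.

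**The concern.** A reader of the finished trial needs to know in advance which result decides whether the programme worked. The two abstract paragraphs give different answers, the outcomes section gives four at once, and neither the analysis plan nor the sample size breaks the tie. A claim of effectiveness could then rest on whichever outcome and visit reaches significance, with an error rate well above the nominal 5%.

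The outcomes are also not interchangeable. Knowledge is what the sessions teach, and the principal investigator reinforces the key points on the first day of each follow-up, so a gain in knowledge is likely. Cotinine measures exposure, the harm the programme is meant to reduce, and is assayed from vials without personal identifiers. As written, a gain in knowledge with no change in exposure could be reported as meeting the aim in the abstract's Design paragraph.

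**Working it through.** **1. Does the sample size reveal the intended outcome?** Inputs from Sample size calculation: d = 0.3, 90% power, 10% attrition, total 250. The level is 0.05; two-sided is assumed because sidedness is not stated.

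- Two-sample comparison: n per arm = 2 × (1.96 + 1.2816)² / 0.3² = 233.5, so 234. The exact t-test gives 235, or 470 in total. With attrition, 235 / 0.9 = 261.1, so 262 per arm and 524 in total.
- Same test, one-sided: 191 per arm, 382 in total, 426 with attrition.
- Paired t-test: 119 per arm. With attrition, 119 / 0.9 = 132.2, so 133 per arm and 266 in total (262 if inflated by 1.1 instead).
- Two-group ANOVA with f = 0.3: about 119 in total. Chi-square with w = 0.3 and 1 df: about 117 in total. Both are before attrition.

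None of these gives 250, so the figure does not show which outcome the trial was built on. That it cannot be reproduced is a separate matter, and this point does not depend on it.

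**2. How many tests could carry the claim?**

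- Outcomes listed under Study outcomes, one visit: cotinine, knowledge, attitude, behaviour = 4.
- The same outcomes over all follow-ups: 3 scales × 3 visits + cotinine once = 10.

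**3. Chance of at least one p < 0.05 when there is no effect, if tests are independent:** 1 − 0.95^m.

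- m = 4: 1 − 0.95⁴ = 18.5%
- m = 10: 1 − 0.95¹⁰ = 40.1%

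**4. Allowing for correlation.** Repeated scores from the same children are correlated, but the article gives no correlations. The ten tests were therefore simulated (300,000 replicates) under assumed values, with cotinine taken as independent of the scores.

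| Between scales | Between visits | Any p < 0.05 | Favouring the intervention |
|---|---|---|---|
| 0.3 | 0.5 | 34.9% | 18.3% |
| 0.5 | 0.6 | 31.5% | 16.2% |
| 0.7 | 0.8 | 24.5% | 12.5% |
| 0.9 | 0.9 | 17.9% | 9.2% |

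If independent, the favourable-direction figure is 1 − 0.975¹⁰ = 22.4%. For comparison, a single test has 5% in either direction and 2.5% in the favourable direction. Per-protocol repeats and subgroups are not counted.

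**5. Power once one between-arm test is named.** Completers per arm: 125 × 0.9 = 112.5, taken as 112. A two-sided t-test at d = 0.3 and 0.05 has 61% power, before any allowance for clustering. Keeping four co-equal outcomes at 12 months with a Bonferroni level of 0.05 / 4 = 0.0125 would give 39% for each.

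**The case against.** The strongest reply has four parts.

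- **The aims are compatible.** A reader might infer that the plan contradicts itself outright. It does not. The abstract's Methods paragraph does not say that cotinine is the only measure, and the abstract's conclusion, the objectives and Study outcomes all join cotinine or exposure with the scores. This stands: the aims are joint and unranked, and the inconsistency is one of emphasis within the abstract.
- **The tests are not listed.** A reader might infer that the plan tests every outcome at every visit, in two populations of equal standing. The article gives one general level and one test for Phase 2; the count of tests is an inference from the measurement schedule. Cotinine has only one post-baseline value, and nothing states the relative standing of the two populations. This also stands, so the error rates describe what the text permits.
- **Larger figures are tempting.** Adding self-efficacy makes 13 tests and 1 − 0.95¹³ = 49%. That needs a scale absent from Study outcomes and full independence. Nor does a per-protocol repeat double the error, since it uses largely the same children. It is also tempting to discount the scores because children know their arm, but the article does not say whether they do.
- **Other documents may rank the outcomes.** Appendix 1 and any SAP are not shown and might name a primary outcome, and correction among secondary outcomes is commonly left to a SAP. This is a fair limit. It does not remove the point, because the shifting aim and the unranked list are stated in the article itself.

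**Conclusion.** The point holds in this form: the article is inconsistent about its deciding outcome, its own outcomes section leaves four unranked, and neither the significance level, the analysis populations nor the effect size identifies a lead analysis. Followed as written, the plan allows a false-positive efficacy claim at 18.5% for four independent outcomes at one visit. For ten tests the figure is 40% if independent and about 18% to 35% under the assumed correlations. Restricted to results favouring the intervention, ten tests give about 9% (highest correlations) to 22% (independence), against a nominal 2.5%.

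These figures assume a valid between-arm test for each comparison, two-sided 0.05, and correlations that the documents do not supply. The use of a paired t-test for Phase 2 and the absence of a clustering allowance are separate questions. The documents do not support calling the aims mutually exclusive or treating 49% as the expected error rate.

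**What to change.** Make these changes before any outcome data are analysed, since a primary outcome chosen after seeing results restores no error control.

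- Name one primary outcome and analysis: the between-arm difference in salivary cotinine at 12 months, by intention to treat. This agrees with the abstract's Methods paragraph and with the Phase 2 eligibility criterion, which is itself a cotinine level.
- Label the questionnaire scores (including self-efficacy, if kept), the 3- and 6-month visits, subgroups and per-protocol results as secondary or supportive. Correction among the secondary outcomes can be left to the SAP.
- State which outcome the 0.3 refers to, and restate the power if it does not hold for the primary comparison.
- Align the abstract, the objectives and any appendix or SAP.

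No new data are needed, but the cost is more than wording. Gains on the questionnaire alone could no longer be claimed as confirmatory. The stated 90% power may also have to be restated less favourably: about 61% for a two-sided between-arm test at d = 0.3 with 112 completers per arm, before clustering.

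### The only Phase 2 test named uses complete pairs, so unless missing values are imputed the analysis labelled intention-to-treat would be a complete-case analysis by assigned arm

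*Protocol article*

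**What the plan says.** Four statements in Materials and Methods of the Protocol article bear on this point.

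- **Analysis sets** (Data analysis plan): "Analysis will be done based on both the Intention to Treat and Per Protocol analysis". Neither set is defined further.
- **Test** (same paragraph): "For the phase 2 study, Paired sample t - test will be done". No other Phase 2 method is named, and the visits to be paired are not stated.
- **Cotinine schedule** (Salivary Cotinine level estimation): exposure is determined by "measuring their salivary cotinine levels twice, one at the end of Phase 1(baseline) and second at the 3rd follow-up, i.e., at 12 months". There is no cotinine sample in between.
- **Sample size** (For phase 2): "We calculated a total sample size of 250 with125 in the control group and 125 in the intervention group", with "90% power, an Effect size of 0.3, confidence interval at 95% and attrition at 10" percent.

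The Questionnaire paragraph schedules the knowledge, attitude and behaviour scores at the start of Phase 1 and at all three follow-ups (3, 6 and 12 months). The Random allocation paragraph says that participants are recruited within clusters and the clusters are then randomised.

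**The concern.** A paired t-test works on within-child differences, so a child with one value missing has no difference to analyse. Because cotinine is measured only once after the intervention, a child who leaves at any time before month 12 has no post-intervention cotinine. The article expects such losses and allows for them in the sample size, but that allowance protects precision only. It does not say how these children enter an intention-to-treat analysis.

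The questionnaire scores raise a related problem. If the paired test compares baseline with 12 months, a child seen at 3 and 6 months who then leaves is dropped, although two post-intervention scores are already in hand.

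What is at stake is the meaning of the intention-to-treat label. If children who leave change differently from those who stay, and if loss or that gap differs between arms, the result is shifted without the label showing it.

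**Working it through.** **1. The plan's own sample size.** Inputs: effect size 0.3 (type not stated), 90% power, alpha 0.05 (taken as two-sided), 10% attrition.

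- Paired t-test, standardised mean change 0.3: 119 pairs per arm; 119 / 0.9 = 132.2, so 133 per arm and 266 in total.
- Two-sample t-test, difference 0.3 SD: 235 per arm; 470 / 0.9 = 522.2, so 523 in total.

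Neither gives 250. The paired test with 112 to 113 complete pairs per arm has 88.2% to 88.5% power, which is close to the stated 90%; with 125 pairs it has 91.4%. The point below does not depend on reproducing 250.

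**2. Children without a cotinine pair.** Expected complete pairs = (1 − 0.10) × 250 = 225, or 112.5 per arm. Children without a pair = 0.10 × 250 = 25.

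**3. Possible bias.** Let p be the fraction lost in an arm and g the mean change of lost children minus that of retained children, in SD of change. The full-arm mean is the retained mean + p × g, so:

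- retained minus full, within an arm = −p × g
- shift in the arm contrast = −(p₁g₁ − p₂g₂)

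The documents give neither the split of losses between arms nor g. Assuming g from 0.25 to 1.0 SD, the sizes of the shift are:

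| Loss in the two arms | g = 0.25 | g = 0.5 | g = 1.0 |
|---|---|---|---|
| Within one arm, 10% | 0.025 | 0.05 | 0.10 |
| Contrast, 10% and 10%, same g | 0 | 0 | 0 |
| Contrast, 15% and 5%, same g | 0.025 | 0.05 | 0.10 |
| Contrast, 20% and 0% | 0.05 | 0.10 | 0.20 |

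Equal loss does not protect the contrast if the gap differs between arms. With 10% lost in each, g = 0.5 in one arm and 0 in the other, the shift is 0.10 × 0.5 − 0.10 × 0 = 0.05 SD.

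**4. Against the planned effect.** If the stated 0.3 is read on the same scale (an assumption), 0.05 / 0.3 = 17% and 0.10 / 0.3 = 33%. To cancel an effect of 0.3 SD altogether at 15% and 5% loss, the common gap would have to be 0.3 / (0.15 − 0.05) = 3 SD.

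**5. Scores.** Under a baseline-to-12-month pairing, a child who leaves after month 6 contributes nothing, although three of the four scheduled scores exist (baseline, 3 and 6 months).

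**The case against.** The strongest reply is that the article is silent on missing data and does not contradict itself. It does not say that incomplete children are deleted, it does not define the intention-to-treat set as completers, and a paired t-test can be run on imputed values. Handling of missing data is commonly left to a fuller protocol or analysis plan, which is not shown. This reply stands against two stronger readings that a reader might infer:

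- **That the intention-to-treat promise is broken, or that the result is bound to be a completers' result.** This follows only if nothing is imputed, and the article leaves that open.
- **That the intention-to-treat and per-protocol sets would coincide.** Even without imputation, a child who missed sessions but gave the 12-month sample stays in the assigned arm.

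Three further objections limit the size of the problem:

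- A tendency for leavers to come from homes with more smoking is a difference in level. If stable, it cancels in a within-child change. Bias needs a difference in change, and the documents give no evidence of one.
- Differential loss is only a possibility. Controls get one education session, but the questionnaire is scheduled at all follow-ups without restriction to one arm, so control schools may be revisited just as often.
- The loss splits and gaps above are assumptions, and 20% against 0% is extreme.

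It is also fair to say that a larger problem lies in the same sentence: a paired test compares before with after within an arm, and so gives no contrast between arms and ignores the clusters. That is a separate matter. Curing it would not by itself settle this one, because a between-arm test of change scores also drops incomplete pairs.

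What remains is more than a request for a missing-data paragraph. The article fixes a specific test that by default discards incomplete children and, for the scores, can discard data already collected.

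**Conclusion.** The point holds in a limited form. As written, and unless values are imputed, about 25 of 250 children would not contribute to the cotinine result. A baseline-to-12-month pairing would also ignore the earlier scores of children who leave later. The intention-to-treat analysis would then be a complete-case analysis by assigned arm.

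The count rests on the plan's own 10% attrition. The bias does not rest on any figure in the documents. Under the assumed splits and gaps it runs from 0 to 0.20 SD for the arm contrast, with 0.05 SD at 15% and 5% loss and a 0.5 SD gap, and it is zero if loss and gap are equal in both arms. A reader might take the 17% or 33% of the planned effect as an estimate of the bias. The documents do not support that, because both inputs are assumed and the type of the 0.3 effect size is not stated.

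The change is worth making because a better method is available at little cost, not because a serious bias has been shown.

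**What to change.** For the intention-to-treat analysis, replace the paired t-test with a linear mixed model in which children are analysed in the arm to which their cluster was assigned. It should have arm-by-time terms, allowance for correlation between repeated values on a child, and a random school effect, since the article states cluster randomisation (the clusters are taken here to be schools). Use all available scores at baseline, 3, 6 and 12 months, and log cotinine at baseline and 12 months.

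Add a delta-shift sensitivity analysis for missing 12-month cotinine: shift the values assumed for missing children by a range of amounts, separately by arm, and report how the arm contrast moves. This is needed because a child with baseline cotinine only adds little to the estimated effect in the mixed model, so for cotinine the model gains little beyond conditioning on baseline. The larger gain is for the scores.

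The cost is changed wording and slightly more analysis work. No extra participants, visits or assays are needed. The main downside is that the mixed model relies on a missing-at-random assumption, which the delta-shift analysis probes for cotinine but cannot verify.
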